#### 6.1.3 Study duration

For the interventional part of the study, we need 24 months; starting in February 2023 (CEC approval provided). The following Table highlights some key time events scheduled for the current study.

| Timetable

P = Spring
S = Summer
A = Autumn
W = Winter | Activity (year)                     | 2023     |          |          |          | 2024     |          |          |          |
|------------------------------------------------------------------------------|-------------------------------------|----------|----------|----------|----------|----------|----------|----------|----------|
|                                                                              | Start schedule February 2023 | P | S | A | W | P | S | A | W |
|                                                                              | Preparations                        |          |          |          |          |          |          |          |          |
|                                                                              | Clinical study                      |          |          |          |          |          |          |          |          |
|                                                                              | Database                            |          |          |          |          |          |          |          |          |
|                                                                              | Interim analysis                    |          |          |          |          |          |          |          |          |
|                                                                              | Monitoring                          |          |          |          |          |          |          |          |          |
|                                                                              | Final analyses and report           |          |          |          |          |          |          |          |          |
|                                                                              | Academic writing of paper           |          |          |          |          |          |          |          |          |
|                                                                              |                                     |          |          |          |          |          |          |          |          |

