The duration of pre-surgical decolonization is planned to be five days. However, when this pre-surgical time period is too short, the decolonization may also start at least 3 days before surgery and be continued up to 2 days post-surgery. During the post-surgery application, the patient will be washed with water and octenisan® by their treating nurses. The patient will also return the empty/used set and answer to a short questionnaire during their hospital stay. The study team will recuperate the questionnaire during hospitalization. We renounce on routine microbiological assessments of skin colonization, but the hospital's infection control can demand it for other reasons regarding infection control. Hence, skin colonization data will only be available for some selected patients that are screened for body carriage of antibiotic-resistant pathogens, according to the infection control recommendations in Switzerland.

There will be a Monitoring at study start, the interim analysis and at the end.

The primary study outcomes are unplanned revision surgery for SSI and wound problems at 42 days for all surgeries; or 1 year in case of an implant-related surgery. Secondary objectives are other unplanned revision surgeries for non-SSI reasons, all adverse events, as well as patient's subjective impression of the decolonization.

The treatment period includes the following daily study visits:

- Visit 1 - Enrollment (Day 1)
- End-of-Treatment (EOT) -Visit is the Day of Surgery or Day 1-2 after surgery
- Test-of-Cure-Visit (TOC) (clinical surgical control) - Day 42 (+/- 14 days)
- Further follow-up (eventually by phone call) for implant-related surgery - 1 year (+/- 2 months)

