#### 3.2.1 Study definitions

An orthopedic infection for this trial is the microbiological evidence of bacteria in at least two intraoperative tissue samples together with radiological (osteomyelitis, collections, inflammation) and/or clinical evidence of infection (pus, discharge, sinus tracts, rubor, calor, pain). Histological proof is facultative for this study. Implants are defined as any implants except for transient wires or fixator pins. A wound problem is any unplanned post-surgical wound pathology leading to surgical revision. Remission of infection is the absence of clinical and/or radiological and/or laboratory signs of (former) infection after the minimal follow-up time of 1 year for implant -related surgery with implants left in place; or two months for implant-free surgery (including surgery when all implants have been removed)..

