## 5. STUDY OUTCOMES

### Primary outcomes:

- Remission (and inversely superficial or deep-space SSI and revision surgeries for non-infected wound problems; composite primary outcome) at 6 weeks (and/or a 1 year for surgeries with implant)

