#### **9.2 Procedures at each visit for both prospective-randomized studies**

At enrollment (Visit 1 / Day 1), patients will be randomized at ratio 1:1 into the investigational group (decolonization) and the control group (no decolonization). The study investigators will instruct the correct decolonization procedure. During the decolonization period, patients can also review the patient information leaflet of the set for details on the decolonization procedure. The questionnaire will be handed over to the decolonization patients.

The treatment period includes the following study visits:

- Visit 1 - Enrollment (Day 1)
- Visit 2 - End-of-Treatment (EOT) -Visit is the Day of Surgery or Day 1-2 after surgery
- Visit 3 - Test-of-Cure-Visit (TOC) (clinical surgical control) - Day 42 (+/- 14 days)
- Follow-up (eventually by phone call) for implant-related surgery after 1 year (+/- 2 months).

During the study visits, we assess the history, wounds, adverse events, and the functional status. We examine the patients according to the orthopedic standard, and add supplementary laboratory exams and radiology, only if clinically indicated.

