| During Study | Spring 2024                   | All subjects: SDV for existence and informed consent
First trial participant and at least 10% of trial participants recruited at the time of the monitoring visit, as far as available: eligibility, primary endpoint, SAEs                                                                                                                                           |
| Study end    | December 2024
January 2025 | Control for completeness of source data                                                                                                                                                                                                                                                                                                                                  |

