### 14.1. Payments

Installments will be paid by February 2023 to a Balgrist funding account:

- By February 2023, CHF 47.500.- (forty-seven thousand five hundred Swiss Francs) by Schülke & Mayr AG, [name], Schweiz

In 2024 (study ending) the remaining CHF 7.500.- (seven thousand five hundred Swiss Francs) will be paid to the Institution's account by Schülke & Mayr AG, [name], Schweiz.

The 550 sets (500 for the study, 50 in reserve) are provided by Schülke Switzerland

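### The dated study end (December 2024/January 2025) comes before the 1-year primary time point of implant episodes from much of the second enrolment year, so calendar and endpoint must be reconciled

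*Protocol*

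**What the plan says.** **Endpoint.** The synopsis (Study Conduct) sets the primary outcome "at 42 days for all surgeries; or 1 year in case of an implant-related surgery". Section 5 reads it "at 6 weeks (and/or a 1 year for surgeries with implant"). Section 3.2.1 defines remission "after the minimal follow-up time of 1 year for implant -related surgery with implants left in place". Section 9.2 schedules "Follow-up (eventually by phone call) for implant-related surgery after 1 year (+/- 2 months"). Section 10.1 gives each implant participant a study duration of 1 year.

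**Calendar.** Section 6.1.3: "For the interventional part of the study, we need 24 months; starting in February 2023 (CEC approval provided"). The synopsis repeats the two-year interventional part, and section 3.1 plans the trial itself over two years. In the monitoring table of 12.3 the study-end row is dated "December 2024 January 2025", and its task is to confirm that source data are complete. Section 14.1 says "In 2024 (study ending) the remaining CHF 7.500". The budget in section 14 has two yearly columns.

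**Missing outcomes.** Section 11.4 treats a patient with missing outcome data as a drop-out. Section 11.3 plans Cox regression for the primary outcome, alongside chi-square-type group comparisons.

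**The concern.** An implant patient operated on in the second half of 2024 cannot have a 1-year outcome by January 2025. If enrolment fills 24 months and the study ends when enrolment does, much of the second year's implant cohort lacks the primary time point when the data are declared complete.

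The 1-year horizon for implants extends observation well beyond 6 weeks, so any event in that interval would be missed in these patients. The documents do not settle how such episodes would be handled. Read literally, 11.4 removes them. Staff might instead count them as event-free after a few weeks. Either route affects the primary comparison, and the first also reduces the number analysed below the planned 500 per arm.

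**Working it through.** **Plan's own figure.** For 10% versus 5% events, 80% power and two-sided 0.05, the pooled two-proportion formula gives 435 per arm uncorrected and 474 with continuity correction. The 474 in section 11.2 is therefore reproduced, on the corrected basis. It is rounded up to 500.

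**Calendar inputs**
- Month 0 is the start of February 2023 (6.1.3). December 2024 to the end of January 2025 is then about month 22 to 24 (12.3).
- Accrual length A is 24 months as stated. The synopsis expects at least 600 includable episodes a year; if all enrol, 1,000 / 600 × 12 = 20 months.
- Required follow-up F is 12 months, or 10 if a contact at the early edge of the window counts (9.2).
- Uniform accrual is my assumption.

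**Formula.** With closure at month C, the share of implant episodes short of F is (A − (C − F)) / A. A cannot exceed C, because nobody enrols after closure.

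| Accrual A | Closure C | F = 12 | F = 10 |
|---|---|---|---|
| 24 | 24 | 12/24 = 50% | 10/24 = 42% |
| 23 (stops at closure) | 23 | 12/23 = 52% | 10/23 = 43% |
| 22 (stops at closure) | 22 | 12/22 = 55% | 10/22 = 45% |
| 20 | 24 | 8/20 = 40% | 6/20 = 30% |
| 20 | 23 | 9/20 = 45% | 7/20 = 35% |
| 20 | 22 | 10/20 = 50% | 8/20 = 40% |

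The range is about 30-55%.

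**When follow-up would have to end.** With 24-month accrual, 24 + 12 = month 36, about February 2026; at the late edge of the window, month 38, about April 2026. With 20-month accrual, 20 + 12 = month 32. All fall after the dated study end.

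**Effect on power if the short episodes are dropped.** The implant share is not given. The German summary says only that orthopaedic operations mostly involve implants. With assumed implant share q and short share s, 500 × (1 − q × s) per arm remain. Power is for 10% versus 5%, two-sided 0.05, without continuity correction:

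| q | s | Per arm | Power |
|---|---|---|---|
| none dropped | – | 500 | 85% |
| 40% | 30% | 440 | about 80% |
| 40% | 50% | 400 | 77% |
| 60% | 50% | 350 | 71% |
| 80% | 50% | 300 | 64% |

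The like-for-like baseline is 85%, not the stated 80%, because 474 was obtained with the correction. On the corrected basis, the 400/350/300 rows give about 72/66/58%.

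**The case against.** The strongest reply is that 1-year follow-up is plainly intended. The sentence in 6.1.3 covers only the interventional part and sets no closing date. Section 10.1 gives implant participants a 1-year study duration, the Study Schedule marks study end in the 1-year column as well, and 9.2 and 9.2.4 require the 1-year contact with no calendar cut-off. Section 1.6 mentions an interim look at about two years, which implies continuation, although 11.3.1 plans only one at one year. Section 14.1 is a payment clause and does not govern database lock. The timetable's bars are not visible, so its 2023-2024 columns do not show when the final analysis was placed.

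All of this stands. A reader might infer that half of the implant outcomes can never be observed; the documents do not support that. They contain two incompatible calendars, and the loss occurs only if the dated end prevails. The dated end cannot simply be ignored, however: 12.3 would check completeness of data that, for many second-year implant patients, could not yet exist.

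A second reply is that Cox regression can use partial follow-up and that 11.4 does not mention administrative censoring. That is fair, but 11.4 exempts nobody whose outcome is missing because the study closed, and a chi-square comparison of proportions has no place for a censored episode.

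Third, 11.3.1 allows about 600 per arm. With half the implant episodes dropped, 600 × 0.80 = 480 remain at a 40% implant share (power about 84%) and 600 × 0.70 = 420 at 60% (about 79%). That increase is optional and meant for a different loss, the one caused by the futility look, but it shows that a fall below 80% is not certain.

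**Conclusion.** The point holds as an internal contradiction on the primary endpoint. The 1-year implant outcome, 24 months of enrolment from February 2023 and a study end in December 2024/January 2025 cannot all be kept.

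Conditional on the stated end, and assuming uniform accrual, about 30-55% of implant episodes would lack their primary time point. Half is the figure for one specific case (24-month accrual, closure at month 24, 12 months required), not a fixed result. Power could stay near 80% (40% implants, 30% short) or fall to about 64% (80% implants, 50% short), against 85% on the same basis. A reader might infer that the trial is underpowered; without a stated implant share the documents do not establish that.

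**What to change.** - In 6.1.3, separate end of enrolment from end of study. Define the latter as the 1-year (+2 months) contact of the last implant episode, about February to April 2026 if enrolment ends in January 2025.
- Bring 12.3 and 14.1 into line with sections 5, 9.2 and 10.1. Place close-out monitoring, database lock and the final primary analysis after that contact.
- Amend 11.4 so that implant episodes with shorter follow-up stay in the Cox analysis, censored at last contact.

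Reading the primary outcome at 6 weeks for every episode would also remove the conflict, but it changes the estimand and gives up the later implant events. I do not propose it.

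**Cost.** The final report comes about 12-14 months later, and some follow-up time falls outside the two-year budget. The 1-year contact is already planned and may be a phone call, so no new procedure is needed.

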## 6.2 Methods of minimizing bias

The methods of minimising bias applied in our study are the randomization to add validity of the statistical tests used to demonstrate significance. The differences between intervention and control groups should behave like differences between two random samples from the population so that they can be compared to what would be expected in the population by chance.

### 6.2.1 Method of assignment to treatment/intervention (randomization, stratification)

After written informed consent given participants will be randomized with a 1:1 ratio in either treatment group. Randomization is done by designated study staff drawing a sealed envelope containing a randomization card or electronically. Patients are informed about the assignment by the investigators.

### 6.2.2 Blinding procedures

There will be no blinding of patients, and no placebos.

## 6.3 Unblinding Procedures

n.a.

## 7. STUDY POPULATION

### 7.1 Eligibility criteria

#### Inclusion criteria:

- Age  $\geq 18$  years
- Patients with an age  $\geq 80$  years (as considered particularly at risk for SSI)
- Elective orthopedic surgery at the Balgrist
- Chronic immune-suppression (diabetes mellitus, active cancer, cirrhosis CHILD C, renal dialysis, untreated HIV disease, medicamentous immune-suppression equivalent to prednisone  $\geq 10$  mg/day)
- Elective surgery in ischemic skin (e.g. major amputations)
- Elective surgery on non-diabetic and non-infected ulcerated skin
- Tumor (oncologic) orthopedic surgery
- ASA-Scores 3-4 points

#### Exclusion criteria:

- Elective revision orthopedic surgery due to orthopedic infection within the last 12 months in the same area of surgery
- Emergency surgery (defined as planned surgery within the next 48 hours)
- Surgery on infected skin; or surgery under antibiotic treatment for any reason
- "Diabetic foot surgery" (distinct clinical entity; defined as below the ankle)
- Body mass index  $\geq 35$  kg/m^2 (anticipated difficulty of effective decolonization)
- Pregnancy (formality reasons)
- Intolerance or allergy to octenidin and/or ingredients in the octenisan® set
- Use of any other topical antiseptic agents other than octenisan® set (except for the duration of one day)
- Patient unable to understand; or under legal guardian for medical decisions
- Anticipated clinical follow-up of less than 6 weeks after surgery.
- ASA-Scores 1-2, and ASA-Score 5 (high risk of postoperative complications)
- Known skin colonization with antibiotic-multiresistant Gram-negative organisms defined by infection control protocols of Switzerland.

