## Study Conduct

The BALGDEC trial is a single-center trial, beginning in February 2023. Only elective surgery patients with a focus on high risk patients for revision and /or SSI according to prior studies will be included, whereas patients with an extraordinary high risk for SSI or impossibility of decolonization will be excluded. At the Balgrist site, this patient population includes: immune-suppressed patients of any type, tumor surgery patients, revision surgery, patients with ASA-Scores 3-4 points or with an age of  $\geq 80$  years; independently of the presence of an orthopedic implant. The operational study team is mainly composed by two infection control nurses, an infectious diseases physician, an orthopedic surgeon with experience in decolonization studies, and the UCAR-team (Unit for Clinical and Applied Research; study nurses).

The infectious control nurses and the infectiologist provide will provide pre-operatively specific instructions regarding the decolonization measure o the patients, and randomize them (1:1) between the presence or absence of the "set" used. The decolonization set will be physically handed over during the inclusion process. The randomization occurs electronically or by prefabricated cards by another study team member not involved in the patient's information process. During decolonization, patients are asked to change the bed linen and underwear every day and not to share towels, clothes and other textiles with their family or pets. They may use their habitual parfums, but must not use other topical antiseptic agents, body lotions or moisturizer during the decolonization period.

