| Number of Participants with Rationale                                 | Postoperative wound problems occur in at least 5% percent of all interventions. Incidence for both, revision surgery and/or SSI, in our selected patient population is set for 10%. We perform a superiority RCT with a power of 80% in favor of the decolonization. With event-free surgeries to 95% in the decolonization arm versus 90% in the standard arm, we formally need 2 x 474 surgery episodes, which we sum up to 2 x 500 surgeries (n = 1'000). A patient can be included several times as long as he/she gets not infected.

At the Balgrist, we perform at least 5000 surgical operations per year (in reality more than 6000). With a very conservative estimation, we see at least 600 surgical episodes per year (12% of surgeries) that can be included; mostly because of the advanced age, diabetes, and high ASA-Scores of our patients. The interventional part of the trial lasts two years; with interim analysis after 1 year (+/- 2 months). An independent advisory board might stop the trial. For the secondary outcomes (adverse events, questionnaire), we do not require a minimal sample size. |                            |                            |          |          |             |          |          |          |                              |              |                            |                            |                     |       |       |   |               |       |       |       |                          |        |        |        |                      |       |       |       |                  |       |     |       |                           |               |               |               |

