#### 8.1.1 Intervention treatment

The duration of pre-surgical decolonization is planned to be five days. However, when this pre-surgical time period is too short, the decolonization may also start at least 3 days before surgery and may be continued up to 2 days post-surgery. In case of post-surgery application, the patient will be washed with water and octenisan® wash lotion by their treating nurses. The patient will also return the empty/used set and answer to a short questionnaire during their hospital stay. The study team will recuperate the questionnaire during hospitalization.

During decolonization, patients are asked to change the bed linen and underwear every day and not to share towels, clothes and other textiles with their family or pets. They may use their habitual perfumes, but must not use other antiseptic agents, body lotions or moisturizer during the decolonization period.

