##### **9.2.1 Enrolment (Visit 1)**

Information collected during routine pre-surgical consultation and during orthopaedic surgery is not study specific. This data will be used as general demographic information and medical history within the study in case of an orthopaedic infection and study participation.

If a patient appears to be eligible the following study-related procedures are performed:

1. Patient information and obtaining written informed consent.
2. Assign a study identification number.
3. Record/complete medical history and demographics.
4. Review inclusion/exclusion criteria.
5. Randomize the patient and handing out of the decolonization set.

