#### 11.3.2 Final analyses

The intent-to-treat (ITT) population will consist of all randomized patients. Patients will be analysed according to treatment group assignment. Patient disposition and baseline characteristics will be based on the ITT population.

The per-protocol (PP) population will consist of all randomized patients who complete the study (or who are otherwise defined as a treatment failure) according to the clinical investigation plan and who have not deviated significantly from the protocol. All efficacy analyses will be repeated using the PP population. Any analysis involving microbiological assessments will exclude patients without an assigned baseline pathogen.

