### 11.4 Handling of missing data and drop-outs

Missing data regarding the outcome parameters and the decolonization will lead to patient dropout of the study. Drop-outs will be reported in the patients & methods section of the publication, drop-out of data will be reported for a minimum of 10 years after study termination or in case of premature termination of the clinical trial. Major deviations from the protocol will be regarded as drop-outs and excluded from both, the ITT and the PP populations. The independent Data Monitoring Committee may help in case of difficult interpretations of the case among the trial investigators.

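### Surgery more than 48 hours ahead is eligible, but the shortest decolonization course described starts three days ahead, so some short-notice episodes may miss that start

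*Protocol*

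**What the plan says.** - **Eligibility.** Section 7.1 and the synopsis exclude "Emergency surgery (defined as planned surgery within the next 48 hours". This line defines an emergency, but no other criterion concerns the time left before surgery. Section 2.7 adds that nothing beyond the inclusion and exclusion criteria is screened for. The study schedule gives a screening window of day -30 to 0, without a minimum.
- **Course.** Five pre-surgical days are planned. When time is short, section 8.1.1 says "the decolonization may also start at least 3 days before surgery and may be continued up to 2 days post-surgery"; the synopsis (Study Conduct) has the same rule. No later start is described.
- **Intent.** The synopsis says that "patients with an extraordinary high risk for SSI or impossibility of decolonization will be excluded". This sets no day limit and is not carried into the formal list in 7.1.
- **Order of steps.** In section 9.2.1 the criteria are reviewed at step 4. Step 5 is "Randomize the patient and handing out of the decolonization set", so decolonization cannot begin before enrolment.
- **Populations.** Section 11.3.2 limits the per-protocol (PP) set to patients "who have not deviated significantly from the protocol". Section 11.4 states: "Major deviations from the protocol will be regarded as drop-outs and excluded from both, the ITT and the PP populations".

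**The concern.** The eligibility limit and the start rule are set at different distances from surgery: 48 hours and three days. An episode in between passes every criterion, yet if allocated to decolonization it may be unable to start on time. The two post-operative days extend the end of the course; they do not move its start.

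Controls have no course to start, so this deviation can arise in one arm only. What follows depends on how a short start is classed:

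1. It stays in both the intention-to-treat (ITT) and PP populations, under-exposed, and may dilute the effect.
2. It stays in ITT and leaves PP as a significant deviation.
3. It counts as a major deviation and, under section 11.4, leaves both populations. Randomised episodes are then removed from one arm of an unblinded trial.

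**Working it through.** **1. Does the gap exist? It depends on the day count.** Two examples, taking the start as the time of enrolment:

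| Episode | Counted in hours (72 needed) | Calendar days (day -3 needed) | Treatment days including day of surgery (3 needed) |
|---|---|---|---|
| Mon 09:00, surgery Wed 10:00 (49 h) | missed | day -2: missed | Mon, Tue, Wed: met |
| Mon 10:00, surgery Thu 08:00 (70 h) | missed | day -3: met | met |

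The third count is possible because the wash is once daily (8.1) and end of treatment may fall on the day of surgery (9.2). The protocol does not say which count applies.

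**2. The plan's own sample size.** Inputs from 11.1 to 11.3: 10% versus 5%, two-sided 0.05, power 80%.

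- Uncorrected: n = [1.960·√(2·0.075·0.925) + 0.842·√(0.10·0.90 + 0.05·0.95)]² / 0.05² = 434.4, so 435 per arm.
- Continuity-corrected: (n/4)·[1 + √(1 + 4/(0.05n))]² = 473.6, so 474 per arm. This is the plan's figure.

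The sample size is not at fault.

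**3. Power at the planned 500 per arm.** Power = Φ[(d − 1.960·s0)/s1], where d is the difference in event rates, s0 the pooled and s1 the unpooled standard error.

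- Uncorrected: s0 = √(0.075·0.925·2/500) = 0.01666 and s1 = √(0.1375/500) = 0.01658. Then (0.05 − 0.03265)/0.01658 = 1.046, giving 85.2%.
- Corrected: replace n by n·(1 − 1/(n·d))² = 500·0.96² = 460.8, giving 82.3%.

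**4. Short starts kept in ITT (routes 1 and 2).** Let f be the share of decolonization episodes affected and b the share of the benefit they keep. That arm's event rate is 5% + 5%·f·(1 − b). The protocol gives no lead-time distribution, so f and b are assumptions.

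| f (of 500) | b = 0, uncorrected | b = 0, corrected | b = 0.5, uncorrected | b = 0.5, corrected |
|---|---|---|---|---|
| 2% (10) | 83.6% | 80.4% | 84.4% | 81.4% |
| 5% (25) | 80.9% | 77.5% | 83.1% | 79.9% |
| 10% (50) | 75.9% | 72.1% | 80.9% | 77.5% |
| Largest f with 80% power | 5.9% | 2.4% | 11.9% | 4.9% |

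**5. Short starts removed (PP in route 2, both populations in route 3).** With 490, 475 or 450 against 500 controls at 5% versus 10%, uncorrected power is 84.8%, 84.2% or 83.1%. The power loss is slight; the issue is bias. Suppose decolonization has no effect and the removed episodes carry risk r. The remaining risk is (0.10 − f·r)/(1 − f), and the apparent benefit is 0.10 minus that:

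| Assumed r | f = 2% | f = 5% | f = 10% |
|---|---|---|---|
| 10% | 0 | 0 | 0 |
| 15% | 0.10 points | 0.26 points | 0.56 points |
| 20% | 0.20 points | 0.53 points | 1.11 points |

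An r below 10% would bias the other way.

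**The case against.** The texts can be read as consistent. The standard course is five days, and the shortened one is three before surgery plus up to two after, again five. On a treatment-day count, a patient enrolled 49 hours ahead fits three washes in, and the 48-hour limit matches the three-day floor. The shortened start is worded as a permission, the synopsis already intends to exclude patients who cannot be decolonized, and section 7.2 places screening at elective pre-surgical consultations. Nothing shows that any episode falls in the window. How deviations are classed is often left to the analysis plan, which is not at hand.

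Much of this stands. A reader might infer that every episode 48 to 72 hours ahead is bound to miss the start; the day-count table shows that this is not so. A reader might also infer that the protocol directs such episodes out of ITT. It does not: neither 11.3.2 nor 11.4 calls a short start significant or major, so route 3 is a possibility. Section 11.4 is also a wider problem that applies to any non-compliance.

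The power argument for a new exclusion is weak as well. If excluded episodes are not replaced, uncorrected power is 84.5%, 83.4% or 81.4% (490, 475 or 450 per arm). Keeping them at half benefit gives 84.4%, 83.1% or 80.9%. If they kept two-thirds of the benefit, keeping them would be better: 84.7%, 83.9% or 82.4%.

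What the objection does not remove is that the literal start rule and the literal exclusion differ, and that no passage reconciles them. Under an undefined count, staff could class the same 50-hour episode as compliant or deviant, in one arm only.

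**Conclusion.** The point holds in a limited form. On the plain wording, some eligible episodes may miss the only start described for a shortened course: most of those about 48 to 72 hours ahead if days mean hours, some if calendar days, few or none if treatment days including the day of surgery. The consequence is confined to the decolonization arm: dilution, or removal from one or both populations, depending on classification.

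The size is unknown and probably small. The shares of 2%, 5% and 10%, the retained benefit and the 15% and 20% risks are all assumptions. On the correction that reproduces 474, a share of 2.4% with no benefit is enough to bring power to 80%, so the margin is thin, but that is a worst case.

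This is a change the sponsor could make, not one the trial depends on. Its main merit is comparability of the arms, not power. A reader might infer that a lead-time check would end short-course deviations; it would remove only those that the eligibility rule itself lets in.

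**What to change.** 1. In 8.1.1, state whether days before surgery are hours, calendar days or treatment days, and whether the day of surgery counts.
2. In 7.1 and the synopsis, keep 48 hours as the definition of an emergency and add an exclusion for planned surgery fewer than three days after randomisation, on the same count.
3. Check it in all patients at step 4 of 9.2.1, before allocation at step 5.

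Late self-starts, incomplete courses and surgery moved forward after randomisation will still occur in one arm, so this does not replace correcting section 11.4.

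**Cost.** One eligibility line, one definition, and a few short-notice episodes lost from both arms. The synopsis says "we see at least 600 surgical episodes per year (12% of surgeries) that can be included", so about 2 × 600 = 1,200 in two years. Losing 2%, 5% or 10% leaves 1,176, 1,140 or 1,080: above the target of 1,000 before refusals, but below the roughly 1,200 (about 600 per arm) that 11.3.1 allows as an extension. If the lost episodes are not replaced (490, 475 or 450 per arm), power is 84.5%, 83.4% or 81.4% uncorrected, and 81.4%, 80.1% or 77.8% with the continuity correction. Replacement is therefore preferable if the share approaches 10%.
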